## Abstract

Background: As a typical high-disability neurodegenerative disease, Parkinson’s disease (PD) progresses variably, and patients who are clinically insensitive to dopaminergic therapy and whose symptoms fail to improve are commonly observed. As a result, achieving early neuron protection is critical. Methods/Design: The NET-PD study is a 2-year prospective single-center, double-blind, multi-arm, delayed-start, sham-controlled clinical trial assessing the long-term neuroprotective effect of intermittent theta burst stimulation (iTBS) in PD patients. Patients diagnosed with PD, aged 50–80, Hoehn–Yahr stage ≤4, and who maintain medication stability during the study will be enrolled. Clinical assessment and multi-modal markers are used to clarify the clinical improvement and dynamic neuronal changes in PD patients. With a standard deviation of 2, a test level of 0.05, a dropout rate of 10%, and a degree of certainty of 0.9, 60 PD patients are required for this study. Results: The NET-PD project was funded in March 2022, data collection began in July 2022, and is currently in the recruitment phase with two PD patients already enrolled. Data collection is expected to be completed in June 2024. The results are expected for publication in December 2024. Discussion: Previous research has demonstrated a rudimentary method for assessing and delaying PD progression in clinical medication trials. The NET-PD study adopts a rigorous methodology and specific disease-modifying designs to demonstrate the neuroprotective effect of iTBS on PD and investigate the potential mechanism of iTBS in regulating brain and motor functions. We hope to provide supposition for the subsequent exploration of diverse neuroprotection methods.

## 1. Introduction

Parkinson’s disease (PD) is a disabling neurodegenerative disease with core clinical features divided into motor symptoms (MS), which are characterized by bradykinesia, resting tremor, myotonia, and postural balance disorders, and non-motor symptoms (NMS), which are characterized by olfactory disturbances, sleep disturbances, autonomic dysfunction, and psychiatric disturbances [1]. The prevalence of PD increases substantially with age, with slightly more men than women. Worldwide statistics show a prevalence of 1–2% in people over 65 and 3–5% in people over 85 [2,3]. PD is currently treated with a combination of pharmacological therapy, surgery, exercise therapy, neuromodulation, psychological support, and caregiving. Pharmacotherapy, represented by carbidopa-levodopa, remains the primary treatment of choice [4]. Despite dopaminergic therapy being the first strategy for PD, patients who are clinically insensitive to medication and whose symptoms fail to improve are commonly seen. Surgical methods such as deep brain stimulation can improve motor symptoms in moderate-to-advanced PD. As a typical high-disability geriatric disease, PD progresses variably, and neither drugs nor surgery can effectively delay or stop the progression of the disease. Therefore, it is of great significance to strive for neuron protection early. Despite a number of large studies, no disease-modifying pharmacologic treatments have been identified at present [5].

With the discovery of structural and functional alterations in specific neural circuits associated with the development of PD, many researchers attempt to use neuromodulation targeting specific brain regions for the treatment of PD and have made some progress. High-frequency repetitive transcranial magnetic stimulation (HF-rTMS, ≥5 Hz), which induces increased local metabolism and enhances cortical activity, is considered as the most promising paradigm for treating motor function in PD [6,7,8,9,10]. As it is a regenerative stimulation pattern with a shorter stimulation duration and more intense stimulation sequence, intermittent theta burst stimulation (iTBS) still induces synaptic plasticity faster when paired with lower stimulation intensity [11]. A 6-hydroxydopamine (6-OHDA)-induced PD rat model revealed that the loss of nigrostriatal dopaminergic neurons was positively correlated with an iTBS-induced reduction in PD motor plasticity, and iTBS could induce the recovery of loss of dopaminergic neurons in substantia nigra [12]. iTBS in the primary motor cortex (M1) significantly improved limbic dyskinesia, reversed the reduction of dendritic spines, enhanced striatal excitability, modulated striatal plasticity, and induced long-time depression (LTD) in the striatum that are sensitive to low dopamine levels [13,14]. Additionally, within the PD rat brain, HF-rTMS synergistically neuronal repair soluble factors caused a favorable microenvironment for the survival of DA neurons with improved motor function [15]. Moreover, long-term iTBS seems to have a synergistic effect with dopaminergic neurotransmission or neuromodulation; specifically, iTBS on the dorsolateral prefrontal cortex increased the ipsilateral theta oscillatory power, which may contribute to the recovery of executive function and working memory [16].

Neuroprotective or disease-modifying therapy can slow or even stop disease progression and prevent the onset of eventual functional disability [17], which is critical for PD patients. Neuroprotective therapy faces a few challenges, the most important of which is the limitation of experimental design. The traditional washout trial design suffers from the disadvantages involved in uncertain washout period and high patient dropout rate [18]. Delayed-start trial designs can largely solve this nuisance. This kind of design eliminates the symptomatic effect brought by treatment itself, enabling more precise monitoring of the “protective effect” results [19]. Moreover, delayed-start design does not need a washout period, which allows more patients to be treated and is more ethical; thus, patients may be more cooperative [20]. Several large cohort studies devoted to neuroprotection and disease modification have initially confirmed the reliability of the delayed-start trial design, and the current results found little disease-modifying effects for most drugs [21,22,23].

To validate the therapeutic effectiveness of iTBS, large randomized controlled studies with long-term follow-up are still needed to validate the results of current studies. Additionally, TMS has not been explored in any study for its neuroprotective effects in PD patients, nor was there definitive evidence of PD neuroprotection. Based on the research background and previous foundation above, NET-PD proposes to adopt a delayed-start randomized double-blind pseudo-stimulation controlled study design to perform multi-sequential M1-iTBS under individual MRI-navigation to explore the ameliorative and neuroprotective effect of long-term treatment with iTBS on PD patients, and to explore the potential mechanism of its therapeutic action by assessing the relationship between dynamic changes in multi-modal indexes and clinical symptoms. The investigators hope to provide a possible way to protect or even reverse neuronal loss in PD and delay the progression of motor disorders in PD.

## 2. Methods/Design

### 2.1. Study Aims

The primary objective of NET-PD is to evaluate the neuroprotective effect of iTBS in PD patients. Secondly, clinical assessment and multi-modal markers are used to clarify the clinical improvement of motor symptoms and dynamic neuronal changes due to iTBS in PD patients, and to provide long-term follow-up evidence for the neuroprotective effect of iTBS. Meanwhile, by analyzing the dynamic changes before and after the treatment, we can explore the potential mechanisms of iTBS regulating brain and motor functions.

### 2.2. Study Design

NET-PD is a 2-year prospective single-center, double-blind, multi-arm, delayed-start, sham-controlled trial. The study is conducted in two stages—the pseudo-controlled and active-treatment stage—with each stage consisting of a 2-week intensive phase and a 12-week maintenance phase, for a total of 14 weeks. The intensive period involves daily or twice-daily iTBS (or pseudo-stimuli) per week, for a total of 10 or 20 sessions, and the maintenance period consists of 12 weeks of iTBS (or pseudo-stimuli) once or twice a day, 2 days a week, for a total of 24 sessions in the single-stimulation group or 48 in the double group. In stage 1 (pseudo-controlled stage), patients are randomly assigned to one of four intervention groups in a 1:1:1:1 ratio: early-start single iTBS group (A1), early-start double iTBS group (A2), delayed-start single iTBS group (S1), and delayed-start double iTBS group (S2). The early-start groups conduct active iTBS throughout, whereas the delayed-start groups use pseudo-stimuli in the first stage and start using iTBS in the second stage. The only difference between the single- and double-stimulation group is the number of sessions per day: once daily for the single group and twice daily for the double group. In stage 2 (active treatment stage), participants in A1 and A2 continue to receive the same iTBS protocol as the first stage, while those in S1 and S2 start to receive active iTBS. All patients are required to have a detailed follow-up clinical assessment and electrophysiology record at baseline, 2 weeks, 14 weeks, 16 weeks, and 28 weeks. MRI and peripheral blood are collected at baseline, 14 weeks, and 28 weeks (Figure 1, Table 1). Each patient will spend 7 months in this study and the total duration of the research will be approximately 2 years, from July 2022 (first in) to December 2024 (last out) (Figure 2).

### 2.3. Inclusion Criteria

Patients entering this study are required to meet all of the following criteria:PD diagnosed according to the revised clinical diagnostic criteria of the Movement Disorder Society (MDS) International (2015 version);Aged 50–80, age of diagnostic ≥50, male or female;Hoehn–Yahr stage ≤4;With or without levodopa, maintaining medication stability during the study period;Good compliance with the long-term intervention and follow-up.

Written informed consent should be signed by each patient; this study has been approved by Ruijin Hospital’s ethical committees.

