### 2.8. Randomization and Blinding

To reduce measurement bias during subjective assessment, we adopt a randomized grouping and double-blind design. Participants are assigned into four arms in a 1:1:1:1 design according to a predetermined generated random number table generated by computer algorithm before the start of the entire experiment. The clinical assessments are scored by specialists not involved in the intervention and grouping, based on the coded and disordered video to ensure the objectivity and authenticity. All the patients are blind to treatment. The pseudo-stimulation coil looks exactly the same as the real iTBS coil and emits the same sound and vibration sensation during the stimulation process, but there is no actual stimulation effect. Coil replacement will be completed before the patient enters the treatment room, which ensures that subjects are unaware of the grouping. Specifically, iTBS operators are unblinded because they need to exchange coils to conduct both active and sham stimuli. Blinding will be evaluated by asking participants to guess group assignment at the end of the whole experiment.

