### 2.17. Sample Size and Statistical Analysis

With reference to data from previous studies published in relevant journals, a total of 60 PD patients are proposed to be enrolled in this single center study. The sample size of this study was calculated based on the improvement in the UPDRS scale after 28 weeks of treatment and differences between groups. Calculations are performed using PASS (Power Analysis and Sample Size) 2008 software (UT, OH, USA), assuming a four-point reduction in the UPDRS at the end of treatment in A1, a five-point reduction in A2, a two-point reduction in S1, and a four-point reduction in S2, with a standard deviation of 2, a test level of 0.05, and a degree of certainty of 0.9 yielded for 13 subjects per group. Considering that the patient dropout rate may be about 10% [24,40], the final plan is to enroll n = 15 cases in each group for n = 60 cases in total. The minimum sample size required to meet the hypothesis of this clinical study is 60, and actual samples of 60 cases or more are in accordance with the clinical study design principles and statistical requirements.

Statistical analysis applies SPSS 20.0 for processing; MRI, EEG, and EMG data are processed on MATLAB platform (Math Works Inc., Natick, MA, USA). All statistics are performed using two-sided tests, and α = 0.05 is the cut-off point used to decide whether the hypothesis is statistically significant. Between-group comparisons of quantitative data will be performed using analysis of variance (ANOVA) or Wilcoxon rank sum test depending on the distribution of the data. A paired *t*-test or Wilcoxon signed-rank test will be used for comparison before and after treatment. Categorical data are tested by chi-square test or exact probability method (if the chi-square test is not applicable).

To compare the changes in UPDRS scores before and after the iTBS intervention at each time point, mainly comparing the differences in their means, two-way repeated-measures ANOVA was used to compare the main effects and the interaction effects between the two for different groups and follow-up points (baseline, week 14, week 28), and post hoc analysis was performed using the Bonferroni test to compare the differences between each follow-up point and baseline scores.

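### Entry is broad in stage and levodopa use, but the stated primary model adjusts for neither, which costs precision and makes a chance imbalance at 15 per arm hard to interpret

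*Protocol article*

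**What the plan says.** Section 2.3 admits patients at "Hoehn–Yahr stage ≤4", aged 50–80, and sets this medication condition: "With or without levodopa, maintaining medication stability during the study period". Section 2.8 describes the allocation as follows: "Participants are assigned into four arms in a 1:1:1:1 design according to a predetermined generated random number table generated by computer algorithm". It mentions neither strata nor minimisation.

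Section 2.17 plans 15 patients per arm, 60 in all. It assumes UPDRS reductions of 4 (A1), 5 (A2), 2 (S1) and 4 (S2) points, "with a standard deviation of 2, a test level of 0.05" and power 0.9. For UPDRS it fixes a two-way repeated-measures ANOVA of group by visit (baseline, week 14, week 28). No term for disease stage or levodopa use appears.

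Table 1 schedules Hoehn–Yahr stage at baseline and medication usage at screening and baseline, so both variables will be on file for every patient.

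**The concern.** Stage and levodopa use could plausibly affect how UPDRS changes over 28 weeks, whether through progression or through response to stimulation. The hypotheses in section 2.16 rest on modest differences in change and slope between arms. If such a factor falls unevenly across arms of 15, part of an observed contrast reflects case mix, and the stated model cannot separate the two.

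Having baseline as a visit deals with differences in UPDRS level. It does not deal with differences in change that go with stage or treatment status. Even in a balanced draw, a prognostic factor left out of the model stays in the residual variance and costs power.

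**Working it through.** **1. The plan's own figure.** One-way ANOVA, four groups, means 4, 5, 2, 4, SD 2, two-sided α 0.05. The overall mean is 3.75 and the sum of squared deviations is 0.0625 + 1.5625 + 3.0625 + 0.0625 = 4.75. The noncentrality is n × 4.75/4. Power is 0.872 at n = 12 and 0.901 at n = 13, so the stated 13 per group reproduces. Allowing for 10% dropout, 13/0.9 = 14.4, which rounds up to 15. The sample-size arithmetic is not in question.

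**2. The contrast at stake.** Early start: (4 + 5)/2 = 4.5. Delayed start: (2 + 4)/2 = 3. The planned difference is 1.5 points, 30 v 30 patients.

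**3. How often imbalance occurs.** The documents give no case mix, so the mixes here are assumptions. With K patients carrying the factor, the number X in the 30 early-start patients is hypergeometric (60, K, 30), and the arms differ by |2X − K|.
- K = 12 at a higher stage: P(difference ≥ 4, i.e. 8 v 4 or worse) = 0.333.
- K = 20 without levodopa: P(difference ≥ 6, i.e. 13 v 7 or worse) = 0.170.

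These count both directions. An excess in the delayed-start arms specifically has half the probability: about 16.7% and 8.5%.

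Across four separate arms with K = 12, some pair differs by 3 or more patients in 63% of allocations. One named pair does so in 26%.

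**4. What imbalance does to the contrast.** Shift = (difference in count/30) × difference in mean UPDRS change between strata. At an assumed 2 points:
- 8 v 4: 4/30 × 2 = 0.27 points.
- 13 v 7: 6/30 × 2 = 0.40 points.

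The planned standard error of the contrast is 2 × √(1/30 + 1/30) = 0.52, so both shifts lie below one standard error.

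**5. Is 2 points compatible with SD 2?** The variance due to a binary factor is p(1 − p)D². For p = 0.2 and D = 2 it is 0.2 × 0.8 × 4 = 0.64, or 16% of the planned variance of 4. For p = 1/3 it is 0.89, or 22%. Both fit.

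**6. What adjustment gains.** Simulated overall F-test at 15 per arm, total SD held at 2. Across the settings simulated for stage differences of 1 to 3 points (40% at the higher stage), type I error was 0.045 to 0.053 with or without the stage covariate. With a 2-point stage difference, power rises from 0.94 unadjusted to 0.97–0.98 adjusted, depending on the assumed share at the higher stage. If stage is not prognostic, power is 0.94 either way.

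**7. Why a main effect is not enough.** With baseline as a visit, a stage main effect s adds the same amount to a patient's week-28 and baseline values. In the change it cancels: (… + s) − (… + s) = 0. Only a stage-by-visit term, or a model for change itself, adjusts the quantity of interest.

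**The case against.** The strongest objection is that this is a condensed article. Strata and block sizes are commonly left to the full protocol and covariates to the analysis plan, and neither is shown. That stands for the allocation. A reader might infer a single unstratified list, but section 2.8 is merely silent. It does not stand for the model to the same degree: section 2.17 names the analysis and its factors, and that stated method can be improved.

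Three stronger readings are tempting, and the documents do not support them.
- **False neuroprotection.** A reader might infer that imbalance would manufacture a spurious effect. Randomisation already allows for chance imbalance, and the error rate stays at its nominal level. A shift arises only in the particular draw and can go either way.
- **A large stratum difference.** Assuming 4 points would double the shifts. But it would take 0.2 × 0.8 × 16 = 2.56 (64%) of the planned variance for stage and 3.56 (89%) for levodopa. Two independent factors of that size would exceed the total. If SD 2 is too small, that is a separate sample-size question.
- **Conflict with an early-disease aim.** The Introduction says "it is of great significance to strive for neuron protection early", but this is background. The objective in section 2.1 concerns PD patients generally, and no hypothesis is confined to early disease.

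It is also fair that the 2-point difference has no source in the documents and that the resulting shifts are smaller than the contrast's standard error.

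**Conclusion.** The point holds as a matter of precision and interpretability. The entry range is wide, the stated primary model uses neither of two plausible prognostic variables that the trial collects anyway, and arms of 15 give limited protection in a single realised trial. On the assumed mixes, splits of 8 v 4 by stage or 13 v 7 by levodopa use, or worse, occur in 33% and 17% of allocations. At an assumed 2-point stratum difference, those two splits move the planned 1.5-point contrast by 0.27 and 0.40 points, that is 18% and 27% of it (0.27/1.5 and 0.40/1.5).

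The case mix and the stratum difference are assumptions. The arm sizes, planned means and SD are the plan's. Neither the validity of the test nor the sample-size arithmetic is challenged.

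**What to change.** Keep the entry range and N = 60. Before any unblinded look at the data, prespecify baseline Hoehn–Yahr stage and baseline levodopa use as covariates for UPDRS change, in one of two forms:
- ANCOVA on change from baseline, with baseline UPDRS, stage and levodopa use as covariates; or
- the repeated-measures model already stated, with stage-by-visit and levodopa-by-visit terms added.

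The sponsor should fix in advance how stage is coded; the documents give no cut-point.

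Optionally, if the list is in fact unstratified, stratify the allocations still to be made by stage (two patients were enrolled at publication). Block sizes should vary at random and be concealed. Section 2.8 states that the operators are unblinded, and in one centre fixed blocks could make later assignments predictable to them. Levodopa use can stay in the model rather than become a second stratum, which limits sparse strata at this size.

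The cost is small. Both variables are already collected. With stage coded in two classes, the ANCOVA uses three degrees of freedom, leaving 60 − 4 − 3 = 53 with all patients evaluable. Stratifying could leave arms off 15 by one or two patients.

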### 2.4. Exclusion Criteria

Subjects meeting any of the following criteria will be excluded from this study:Presence of any of the features that rules out PD (e.g., unequivocal cerebellar abnormalities, downward vertical supranuclear gaze palsy, selective slowing of downward vertical saccades etc.);Patients with severe mental illness or neurological disorders (e.g., epilepsy, cerebrovascular accidents, etc.) or a history of traumatic brain injury or brain surgery;Patients with significant cognitive impairment (MMSE <24) or inability to complete questionnaires independently;Previously treated with TMS, deep brain stimulation (DBS) or spinal cord stimulation (SCS);Have any physical illness that can precipitate epilepsy or intracranial hypertension, including cardiovascular and respiratory disease;Have human implantable materials such as intracranial stents, pacemakers, coronary stents, cochlear implants, etc.;Are currently taking other investigational drugs or participating in other clinical trials;Any other condition that the investigator deems unsuitable for this study.

### 2.5. Withdrawal Criteria

Subjects may withdraw at any time if anything occurs that may jeopardize their interests. Subjects who discontinue the study will no longer be covered by continued data collection. The reason for termination or withdrawal should be documented in the case report form. Patients should withdraw from the trial immediately if they meet the following criteria:Poor compliance to the protocol;Occurrence of an intolerable adverse event;Patients decline further treatment or follow-up;Loss of visits due to unavoidable situations, such as death;The investigators terminate the subject’s continued participation after review.

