### 2.6. Endpoint Criteria

Participants are considered to have completed the experiment when they finish all treatments and assessments or withdrew from the experiment for any reason midway through.

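### Patients who stop or poorly follow iTBS are withdrawn from the trial and no longer measured, so the week-28 UPDRS comparison rests on those who remain

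*Protocol article*

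**What the plan says.** Section 2.5 (Withdrawal Criteria) ends measurement at discontinuation: "Subjects who discontinue the study will no longer be covered by continued data collection". The list of reasons for leaving starts with compliance: "Patients should withdraw from the trial immediately if they meet the following criteria:Poor compliance to the protocol". It goes on to an intolerable adverse event, then "Patients decline further treatment or follow-up", then loss of visits through unavoidable events such as death, and finally "The investigators terminate the subject’s continued participation after review". The reason for leaving is to be recorded in the case report form.

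Section 2.6 (Endpoint Criteria) treats participants as having completed the experiment when they "finish all treatments and assessments or withdrew from the experiment for any reason midway through".

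Section 2.15 makes the between-group difference in UPDRS change the primary outcome. Section 2.16 expects less deterioration from baseline to week 28 with early start than with delayed start. Section 2.17 analyses UPDRS by two-way repeated-measures ANOVA over baseline, week 14 and week 28. Its only provision for dropout is to enrol 15 instead of 13 per group.

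**The concern.** Three of the listed reasons (poor compliance, an intolerable adverse event, refusal of further treatment) concern how the patient takes or tolerates treatment, and a fourth is the investigator's discretion. None of them prevents a later UPDRS assessment. Section 2.5 nevertheless makes each a reason to leave the trial, and leaving ends data collection. The later UPDRS is therefore lost by rule, not by chance.

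A delayed-start design is sensitive to this. The inference at week 28 needs the early-start and delayed-start patients still under observation to be as comparable as they were at randomisation. The arms differ in ways that could affect who leaves: sham against active stimulation in stage 1 for early versus delayed start, and sessions per day for single versus double stimulation. If leaving is also related to outcome, the observed difference mixes treatment effect with selection, and could be too large or too small.

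An analysis plan can choose an analysis set or a missing-data method. It cannot recover outcomes that the protocol says will not be collected.

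**Working it through.** **The plan's own sample size (section 2.17).** Inputs: UPDRS reductions of 4 (A1), 5 (A2), 2 (S1) and 4 (S2), SD 2, α 0.05, power 0.90.

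- Grand mean = (4 + 5 + 2 + 4)/4 = 3.75.
- Squared deviations: 0.0625 + 1.5625 + 3.0625 + 0.0625 = 4.75.
- One-way ANOVA noncentrality λ = n × 4.75/2², with 3 and 4n − 4 degrees of freedom.
- Power is 0.872 at n = 12 and 0.901 at n = 13, so 13 per group is reproduced.
- Dropout: 13/0.90 = 14.4, rounded up to 15 per group and 60 in total. This is also reproduced.

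The arithmetic is sound. It allows for fewer observed patients, but not for those patients being a selected group. If all 15 per group were measured, power would be 0.943.

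**Reference effect.** Early start: (4 + 5)/2 = 4.5. Delayed start: (2 + 4)/2 = 3.0. Difference: 1.5 points.

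**Shift in one arm's mean.** The documents give no dropout by arm and no correlation between dropout and outcome, so both are assumed. With dropout proportion d, correlation ρ between a normal dropout tendency and a normal outcome, and z the (1 − d) normal quantile, the mean of those who remain moves by ρ × SD × φ(z)/(1 − d).

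- d = 0.10: φ(z) = 0.1755, so the shift is ρ × 2 × 0.1755/0.90 = 0.39ρ.
- d = 0.20: φ(z) = 0.2800, so the shift is ρ × 2 × 0.2800/0.80 = 0.70ρ.

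| Dropout in the arm | ρ = 0.3 | ρ = 0.5 | ρ = 1 (limit) |
|---|---|---|---|
| 10% | 0.12 | 0.20 | 0.39 |
| 20% | 0.21 | 0.35 | 0.70 |

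Against 1.5 points, the values at ρ = 0.3 and 0.5 are 8% and 13% at 10% dropout, and 14% and 23% at 20%. These are shifts in one arm's mean. They affect the contrast only to the extent that the other side does not shift equally.

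**Type I error.** Simulation of pooled early versus delayed start, 30 against 30, SD 2, no true effect, two-sided t-test on those who remain, 8,000 runs.

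| Dropout, early / delayed | ρ = 0.3 | ρ = 0.5 | ρ = 1 |
|---|---|---|---|
| 10% / 10% | 0.045 | 0.047 | 0.050 |
| 5% / 15% | 0.055 | 0.057 | 0.102 |
| 0% / 20% | 0.069 | 0.093 | 0.270 |

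The simulation standard error near 0.05 is √(0.05 × 0.95/8,000) ≈ 0.0024, so differences of a few thousandths are noise. Equal dropout leaves the test at its nominal level. Inflation becomes material only when dropout differs markedly between the sides and is clearly related to outcome.

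**The case against.** The strongest reply is that no bias has been shown. Patients are blinded with matched coils (sections 2.8 and 2.9), the expected dropout is only about 10%, and equal dropout mechanisms leave the early-versus-delayed test intact. The sentence quoted from section 2.5 also speaks of leaving the study, not of stopping treatment. The first part stands as a limit on size. The second does not remove the point, because the same section makes poor compliance and refusal of further treatment reasons for leaving the trial.

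Several stronger readings are tempting, and the documents do not support them:

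- **Medication change as a removal rule.** Section 2.3 requires "With or without levodopa, maintaining medication stability during the study period", which can be judged only after entry. A reader might infer that a medication change ends participation. It is not among the reasons listed in section 2.5. Table 1 also already schedules medication usage at every visit, and compliance at baseline, week 14 and week 28.
- **Session burden biasing early versus delayed start.** Single arms have 2 × (10 + 24) = 68 sessions and double arms 2 × (20 + 48) = 136. A1 matches S1 and A2 matches S2, so this is balanced across that contrast. It bears on single versus double stimulation only. Treatment days are equal there too, since double sessions fall on the same day.
- **A bias of about a third of the effect.** Suppose 2 of 15 patients are lost in each delayed arm, none in the early arms, and those lost would have done 4 points worse. The shift is then 2/15 × 4 = 0.53, or 36% of 1.5. At SD 2 under normality, removing exactly the worst 2/15 gives a gap of only about 3.7 points and a shift of about 0.50. The 4-point case therefore goes beyond perfect outcome-based removal.
- **Completion by definition.** Section 2.6 can be read as making completion 100% and contradicting the 10% dropout allowance. No analysis in sections 2.15 to 2.17 uses that definition, and section 2.17 treats dropout separately. It is loose wording that marks the end of participation and does not itself cause selection.

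**Conclusion.** The point holds as a defect in who is measured. Section 2.5 turns stopping or poorly following iTBS into the end of UPDRS measurement, so the week-28 comparison rests on those who remain. Bias is possible, but the documents settle neither its direction nor its size. At correlations of 0.3 to 0.5 it is modest in one arm: about 0.12 to 0.20 points at 10% dropout and 0.21 to 0.35 at 20%. It largely cancels if the mechanism is the same in all arms.

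These figures rest on assumed dropout rates, assumed correlations, normality and the planning SD of 2. A reader should not conclude that the week-28 result will be biased, or that the sample size is wrong. The case for change is that the loss is imposed by rule, cannot be repaired in the analysis and is cheap to avoid.

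**What to change.** Leave the treatment-stopping criteria in section 2.5 unchanged, but separate stopping iTBS from leaving the study. State that the scheduled UPDRS assessments, at least at weeks 14 and 28, continue for every randomised patient who has not refused follow-up, including poor compliers. State also that these data are analysed in the arm to which the patient was randomised.

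As a minor accompanying edit, reword section 2.6 so that withdrawal marks the end of participation and is not counted as completion. Completion can be defined as having a week-28 UPDRS.

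The cost is an amendment and a few extra visits, with no new procedure. At the planned dropout, about 0.10 × 60 = 6 patients are concerned. Fewer than that can be recovered, because death and refusal of follow-up remain losses. Section 3 reports two patients enrolled at the time of writing, so an early change would have applied to nearly the whole sample.
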